**Figure 2. F2:**
[figure not shown]
Schedule for data collection. *1: If adverse events associated with the procedure are suspected to have occurred, an emergency medical examination is performed as necessary. *2: within 28 days before registration. *3: within 120 days before registration.

### 2.10. Ethics approval and patient consent

The study protocol has been approved by the Ethics Committee of Wakayama Medical University (No. W-29), which confirmed that the protocol conformed to the tenets of the Declaration of Helsinki and Ethical Guidelines for Medical and Health Research involving Human Subjects. The trial has been registered with the Japan Registry of Clinical Trials (trial registration: jRCTs052190089). Written informed consent will be obtained from all patients enrolled in the study.

## 3. Statistical analysis

### 3.1. Sample size calculation

A single-center comparative study, in which 50 patients undergoing colorectal ESD were randomized, 27 to the S-O clip group and 23 to the conventional ESD group, found that the procedure time was significantly shorter in the S-O clip than in the conventional ESD group (37.4 ± 32.6 vs 67.1 ± 44.1 minutes, *P* = .03). Similarly, a previous study at Wakayama Medical University of patients who underwent treatment by a single surgeon found that the mean procedure time was shorter in the 57 patients who underwent colorectal ESD with the S-O clip (85.2 ± 52.3 minutes) than in the 42 patients who underwent conventional ESD (104.1 ± 60.3 minutes), although the difference was not statistically significant. Based on self-experimental data, the required number of cases was calculated to be 192 for exploration (significance level 0.1, power 0.8) and 324 for validation (significance level 0.05, power 0.9), with the required number of cases set at 200.

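### The totals of 192 and 324 reproduce only with the smaller S-O clip SD (52.3) in both arms; with both reported SDs, 200 patients give about 76-77% power at two-sided 0.10, not 80%

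*Protocol article*

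**What the plan says.** Section 3.1 (Sample size calculation) cites two sources of planning data. One is an external single-centre randomised study. The other is a single-surgeon series at the lead institution, with "57 patients who underwent colorectal ESD with the S-O clip (85.2 ± 52.3 minutes") and "42 patients who underwent conventional ESD (104.1 ± 60.3 minutes"). The size is then tied to the institution's own series: "Based on self-experimental data, the required number of cases was calculated". Two totals follow, given as "calculated to be 192 for exploration (significance level 0.1, power 0.8) and 324 for validation (significance level 0.05, power 0.9"), and the paragraph ends "with the required number of cases set at 200".

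The section does not name the SD, the test or the sidedness. It claims no variance reduction from covariates. Section 2.2 gives 1:1 allocation.

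**The concern.** The variance of a difference between two means depends on the variance in each arm. The paragraph reports two different SDs, 52.3 and 60.3, so a calculation from these data should reflect both. If only the smaller one was used, the required number is too low and the power of the chosen number is overstated.

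The text reads as though 200 patients exceed the exploratory requirement by 8 (200 − 192). If both SDs are needed, 200 falls short of that requirement, and the stated 80% power on the primary endpoint is not supported by the trial's own inputs. The 324 would be too low in the same way for anyone who relies on it.

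**Working it through.** **Inputs (section 3.1 unless stated)**
- Difference: 104.1 − 85.2 = 18.9 minutes; 18.9² = 357.21
- SDs: 52.3 (clip, n = 57) and 60.3 (conventional, n = 42)
- Exploration: alpha 0.1, power 0.8. Validation: alpha 0.05, power 0.9
- Allocation 1:1 (section 2.2); planned total 200, so 100 per arm
- Assumption: two-sided testing, since sidedness is not stated

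**Formula.** Normal approximation per arm: n = 2(z₁₋α/₂ + z_power)² SD² / difference². The multiplier 2(z + z)² is 2(1.645 + 0.842)² = 12.365 for exploration and 2(1.960 + 1.282)² = 21.015 for validation (unrounded z values). The t-test version uses the noncentral t distribution and adds about one patient per arm.

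**Step 1: reproduce the plan's figures.** With SD 52.3 in both arms, SD²/difference² = 2735.29/357.21 = 7.657.
- Exploration: 12.365 × 7.657 = 94.7, so 95 per arm (190). Noncentral t: 96 per arm, **192**.
- Validation: 21.015 × 7.657 = 160.9, so 161 per arm (322). Noncentral t: 162 per arm, **324**.

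Both match the article exactly under the t-test. The common SDs that return both totals under that test lie between about 52.2 and 52.3.

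**Step 2: use both SDs.**
- Average variance (1:1): (2735.29 + 3636.09)/2 = 3185.69, SD 56.4; 3185.69/357.21 = 8.918. Exploration: 12.365 × 8.918 = 110.3, so 111 per arm. Validation: 21.015 × 8.918 = 187.4, so 188 per arm (189 by noncentral t).
- Pooled by degrees of freedom: (56 × 2735.29 + 41 × 3636.09)/97 = 3116.04, SD 55.8; 3116.04/357.21 = 8.723. Exploration: 107.9, so 108 per arm (109 by noncentral t). Validation: 183.3, so 184 per arm (185 by noncentral t).

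**Step 3: power at the fixed totals.** For 100 per arm with SD 56.4, the standard error is 56.442 × √(2/100) = 7.982, so 18.9/7.982 = 2.368 and power ≈ Φ(2.368 − 1.645) = Φ(0.723) = 76.5%. The noncentral t gives 76.3%, and a simulation with the two unequal SDs gives 76.1%.

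All results by noncentral t, two-sided:

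| SD used | Exploration N | Validation N | Power, N = 200, alpha 0.10 | Power, N = 324, alpha 0.05 |
|---|---|---|---|---|
| 52.3 in both arms | 192 | 324 | 81.6% | 90.0% |
| Pooled, 55.8 | 218 | 370 | 77.1% | 86.0% |
| Average variance, 56.4 | 222 | 378 | 76.3% | 85.2% |
| 60.3 in both arms | 254 | 430 | 71.4% | 80.3% |

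**Step 4: other readings.** None gives both totals:
- one-sided, SD 52.3: 140 and 264
- one-sided, average-variance SD: 162 and 308
- one-sided, SD 60.3: 186 and 352
- 57:42 allocation with the average-variance SD: about 226 and 384
- log-normal scale: 164 and 276
- external randomised study (difference 29.7): 44 and 72

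**The case against.** The arithmetic is not in dispute; the case against concerns certainty and weight.

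- **The SD is inferred.** This stands: the article never names it. Nor are the two matches independent, because both totals depend on the single ratio difference/SD, here 18.9/52.3 = 0.361. A difference of about 20.4 with SD 56.4, or 20.2 with SD 55.8, would give the same pair. Those differences are not in the document, however. SD 52.3 with 18.9 is the only pairing of printed inputs that fits.
- **The planned analysis is adjusted.** Section 3.2.1 specifies regression on the allocation factors. If these explain about 10% of the variance (200/222 = 0.90), or 8% with the pooled SD (200/218 = 0.92), then 200 patients regain 80% power. That is plausible, and it limits the practical harm. But section 3.1 claims no such gain, and the exact match to an unadjusted t-test suggests that none was used.
- **The SDs are imprecise.** They come from one surgeon's 57 and 42 patients, so a true SD near 52 cannot be excluded. This is a reason to present the power as a range. It does not justify applying the smaller estimate to both arms without saying so.
- **The 324 is not this trial's target.** True, and the article mentions no follow-on trial. The error in that figure matters less than the one in the power of 200.
- **An article condenses the protocol.** That would excuse a missing SD or sidedness. It does not excuse printed inputs and outputs that disagree.

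**Conclusion.** The concern holds. From the data on which section 3.1 says it is based, the exploratory requirement is 218-222 rather than 192, so the target of 200 is 18-22 patients below it rather than 8 above. Power at 200 patients and two-sided 0.10 is 76-77%, about 3-4 points under the stated 80%. The validation figure is 46-54 patients too low (370-378 against 324), and 324 patients give 85-86% power, not 90%.

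These results assume two-sided testing, 1:1 allocation, a difference of 18.9 minutes, an unadjusted comparison of means, and no allowance for dropout or for the switching permitted in section 2.6. If alpha 0.1 were one-sided, 200 patients would have about 86% power with both SDs, but the printed totals cannot then be reproduced. The error is modest and in the favourable direction. It does not by itself invalidate the trial.

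**What to change.** Keep 200 patients and correct section 3.1:

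1. State the test, the sidedness, the assumed difference (18.9 minutes) and the SD used. Confirm whether 52.3 was applied to both arms.
2. Replace 192 and 324 with totals based on both SDs: about 222 and 378 with the average variance, or 218 and 370 if the pooled SD is preferred.
3. Restate the power of 200 patients as about 76% (77% with the pooled SD) at two-sided 0.10. If a gain from covariate adjustment is to be claimed, state the assumed share of variance explained.

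The cost is wording only. The stated power becomes slightly less favourable, and no extra patients are needed.

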### 3.2. Statistical analysis

#### 3.2.1. Evaluation of the primary endpoint.

Multiple regression analysis will be performed using procedure time (i.e., from the start of localization to the completion of detachment) as response and allocation group and allocation factor as covariates. Point estimates, 95% confidence intervals, and *P* values for between-group differences will be calculated. In addition, summary statistics (mean, standard deviation, minimum, median, maximum) of treatment duration will be calculated for each group or ESD surgeon (trainee/expert).

#### 3.2.2. Evaluating secondary endpoints.

The complication rate will be defined as the rate of complications associated with the procedure. The frequencies and percentages of complications associated with the procedure, as well as the batch resection, cure, conversion, and adverse event rates will be tabulated for each group. Summary statistics (mean, standard deviation, minimum, median, maximum) from the time of S-O clip traction to the completion of dissection will be calculated for the S-O clip group.

### 3.3. Monitoring

The Monitoring Committee will collect information on patient enrollment, inclusion/exclusion criteria, and serious adverse events and provide feedback to participating sites on any problems for early resolution.

### 3.4. Adverse event reporting

An AE will be defined as any unfavorable or unintended injury or sign, including abnormal laboratory values, that occurs in any subject, regardless of whether or not it is causally related to the study and protocol treatment. Exacerbations of preexisting disease during the protocol treatment period will be regarded as AEs. Data on all AEs occurring between the start of treatment and the last observation specified in the protocol will be recorded. Serious AEs will be defined as deaths, life-threatening AEs, AEs requiring hospitalization or prolonged hospitalization for treatment, permanent or marked disability or dysfunction, or birth defects in offspring.

## 4. Discussion

ESD is a well-established technique that enables en bloc resection regardless of the size and morphology of the lesion.^[16–18]^ Although improvements in endoscopists’ skills and endoscopic equipment have increased the use of ESD for lesion removal, endoscopic manipulation remains difficult, with slight manipulations associated with a risk of complications. Perforation during colorectal ESD can cause peritonitis and require emergency surgery, emphasizing the importance of improving safety. Risks of perforations are higher when lesions are located vertically rather than tangentially, because, in the former, the tip of the knife approaches the submucosa perpendicularly. Safe and rapid dissection requires maintenance of an appropriate submucosal view that is as parallel to the muscle layer as possible. Thus, lesions require pulling in an effective direction. Conventional ESD uses a gravitational traction method that relies on changes in posture. Because this conventional method often cannot maintain sufficient traction, it often fails to maintain an appropriate submucosal view. This increases the difficulty of procedure increases, leading to an increased risk of complications. ESD using the S-O clip uses an endoscope and an independent device to maintain sufficient traction of the lesion in a short time regardless of lesion location. It has the advantage of allowing free manipulation of the scope.

This multicenter randomized controlled trial will evaluate the usefulness of the S-O clip in colorectal ESD by comparing the procedure time and frequency of complications with those obtained during conventional colorectal ESD. If use of the S-O clip shortens the procedure time and reduces the frequency of procedural complications, it may contribute not only to reducing the physical burden on patients, but also to shortening hospital stays and lowering costs. Although the number of facilities that can perform colorectal ESD is currently limited, safer performance of this procedure will allow it to become more widely performed. The major limitation of this trial will be that the operator will not blinded to treatment group allocation.

## 5. Conclusion

This prospective randomized clinical trial at 4 medical institutions has been designed to compare the efficacy and safety of colorectal ESD using the S-O clip with conventional ESD for colorectal epithelial neoplasia. ESD using the S-O clip may shorten procedure time, reduce the incidence of AEs, and standardize procedure. This study should resolve the clinical questions of whether ESD using the S-O clip is safer and more effective than conventional ESD for colorectal epithelial neoplasia.
